## Abstract

**Background:**

Increasing participation in the Australian National Bowel Cancer Screening Program (NBCSP) is the most efficient and cost-effective way of reducing mortality associated with colorectal cancer by detecting and treating early-stage disease. Currently, only 44% of Australians aged 50–74 years complete the NBCSP. This efficacy trial aims to test whether this SMS intervention is an effective method for increasing participation in the NBCSP. Furthermore, a process evaluation will explore the barriers and facilitators to sending the SMS from general practice.

**Methods:**

We will recruit 20 general practices in the western region of Victoria, Australia to participate in a cluster randomised controlled trial. General practices will be randomly allocated with a 1:1 ratio to either a control or intervention group. Established general practice software will be used to identify patients aged 50 to 60 years old who are due to receive a NBCSP kit in the next month. The SMS intervention includes GP endorsement and links to narrative messages about the benefits of and instructions on how to complete the NBCSP kit. It will be sent from intervention general practices to eligible patients prior to receiving the NBCSP kit. We require 1400 eligible patients to provide 80% power with a two-sided 5% significance level to detect a 10% increase in CRC screening participation in the intervention group compared to the control group. Our primary outcome is the difference in the proportion of eligible patients who completed a faecal occult blood test (FOBT) between the intervention and control group for up to 12 months after the SMS was sent, as recorded in their electronic medical record (EMR). A process evaluation using interview data collected from general practice staff (GP, practice managers, nurses) and patients will explore the feasibility and acceptability of sending and receiving a SMS to prompt completing a NBCSP kit.

**Discussion:**

This efficacy trial will provide initial trial evidence of the utility of an SMS narrative intervention to increase participation in the NBCSP. The results will inform decisions about the need for and design of a larger, multi-state trial of this SMS intervention to determine its cost-effectiveness and future implementation.

**Trial registration:**

Australian New Zealand Clinical Trials Registry ACTRN12620001020976. Registered on 17 October 2020.

## Administrative information

Note: the numbers in curly brackets in this protocol refer to SPIRIT checklist item numbers. The order of the items has been modified to group similar items (see http://www.equator-network.org/reporting-guidelines/spirit-2013-statement-defining-standard-protocol-items-for-clinical-trials/).

## Introduction

### Background and rationale {6a}

Australia and New Zealand have some of the highest rates of colorectal cancer (CRC) in the world [1]. In 2019, CRC was the fourth most commonly diagnosed cancer and the second commonest cause of cancer death in Australia. Currently, 40% of CRC is diagnosed at a late stage, leading to a poorer prognosis and outcome [2]. The simplest and most cost-effective method for reducing mortality from CRC is to detect precancerous or early disease through screening with a self-collected immunochemical faecal occult blood test (‘FOBT’) [3].

The Australian Government implemented a National Bowel Cancer Screening Program (NBCSP), sending people aged between 50 and 74 years a free home-based FOBT test kit every 2 years [4]. Despite the ease of access to the NBCSP testing kit, participation is low; only 44% of people return the completed kit. Women are more likely to complete the kit than men (46% compared with 41%) and older people are more likely to complete the kit than younger people (54% of 70 to 74 years old compared with 34% of 50 to 54 years old) [5]. Increasing participation in the NBCSP is a major Australian Government Health Department priority and has potential to significantly reduce morbidity and mortality associated with CRC as well as reduce unnecessary costs [6]. An increase in uptake of screening from 44 to 60%, will prevent 37,300 bowel cancer cases and 24,800 bowel cancer deaths and increasing participation in the NBCSP from 40% to 60% is estimated to reduce annual expenditure associated with CRC by a cumulative $AUD 1.7 billion up to 2030 and $AUD 2.1 billion between 2030 and 2040 [6].

The NBCSP involves primary care (‘general practice’) in the screening program only indirectly through the notification of tests and follow-up of positive results. There is strong evidence to suggest that GP endorsement of screening can increase participation in the NBCSP [7–9]. In Australia, four in five Australians have an episode of care with their GP annually [10], providing an opportunity to discuss CRC screening. To improve care and optimise GP time, general practices are increasingly using short messaging service (SMS) platforms linked to Electronic Medical Records (EMR), mainly to prompt and remind patients about appointments and routine health checks [11]. These messages, delivered directly to patients’ mobile phones, are considered a trustworthy source of health information by patients [12]. Communicating with the patients through SMS has many benefits. A message can be delivered in real time, can be accessed at the patient’s convenience on multiple occasions, and is sent to an individual’s personal device, so it is private and discreet [13]. SMS technology is increasingly being used regularly by older Australians with 82% of 50 to 60 years old accessing a smartphone daily [14]. Furthermore, the use of SMS to remind patients to complete the British Bowel Cancer Screening Program was found to be effective among patients aged 50 receiving a FOBT kit for first time [15].

Other methods that have demonstrated effectiveness at increasing the NBCSP uptake include using narrative communication or “storytelling” as a way of delivering a health promotion message. The Cancer Council of Victoria conducted a television advertising campaign using a highly relatable person talking positively about doing the NBCSP kit which resulted in an increased uptake of testing by 11%, with the highest impact among people who had never been screened or were not up to date with screening [16]. Another method demonstrated to increase screening by reducing apprehension about completing the test, especially self-collecting a faecal sample, has been to provide practical, easy-to-follow instructions about how to complete the NBCSP kit [17, 18].

These single interventions have had small effects on screening uptake [16, 19, 20]. This trial tests a combination of the four interventions within a single SMS (the ‘SMARTscreen intervention’) including (1) a GP endorsement of CRC screening, (2) video stories from relatable people who have had a positive experience about doing the test, (3) an advance notification video about how to complete the FOBT kit, and (4) information about the benefits of CRC screening and the NBCSP. The SMS is targeted to patients aged 50 to 60 years directly from their general practice as they are less likely to participate in screening, more likely to use smartphones, and evidence suggests once someone has done the NBCSP kit once, they are more likely to do it again [5]. The SMARTscreen trial aims to test the efficacy, feasibility, and acceptability of sending the SMARTscreen intervention as a prompt to patients prior to receiving their NBCSP kit on uptake of completing the kit.

### Objectives {7}

The primary objective is to test the efficacy of the SMARTscreen intervention on participation in the NBCSP up to 12 months in people aged 50 to 60 years who are due to receive an FOBT kit from the NBCSP compared to those who receive usual care.

The secondary objective is to determine the feasibility and acceptability of the SMARTscreen intervention from the general practice staff as well as the patients’ perspectives by conducting a process evaluation.

#### Hypotheses

The use of a narrative SMS delivered to patients aged between 50 and 60 years old and due for colorectal cancer screening from their general practice, just prior to receiving the NBCSP FOBT testing kit, will increase the likelihood of completing the kit compared to usual care.

### Trial design {8}

We will conduct a superiority cluster randomised controlled efficacy trial to test if patients in the general practices who receive the SMARTscreen intervention are more likely to complete the NBCSP kit compared with patients in the control group general practices. The unit of randomisation will be the general practice allocated in a 1:1 ratio to either the intervention or control group stratified by practice location and practice size.

Embedded in the trial will be a process evaluation using quantitative and qualitative methods. The quantitative measures will include the number of people who view each of the four individual intervention components of the SMARTscreen SMS and how often they view them. The qualitative research will explore the feasibility and acceptability of the intervention by general practice staff (including GPs, practice managers, nurses, other administrative staff) and patients. This will be done using semi-structured interviews with staff and patients about their experience of sending SMS intervention monthly to their patients (staff) or receiving the SMS (patients).

## Methods: Participants, interventions and outcomes

### Study setting {9}

The SMARTscreen trial will be conducted in general practices located in the Western Victorian Primary Health Network (WVPHN) [21] catchment in Victoria, Australia, which includes a mix of regional cities and towns, and socio-economic and demographic diversity. The population of the WVPHN catchment includes 618,000 people, of which 190,934 (30.4%) are between 50 and 74 years old, the age targeted by the NBCSP [22, 23]. The WVPHN is also a partner in this study.

### Eligibility criteria {10}

#### Inclusion criteria for general practices

General practices will be eligible to participate in the SMARTscreen trial if they are located in the WVPHN region, their electronic medical record (EMR) system is compatible with the Pen CS CAT4 clinical audit tool software (CAT: Pen Computer Systems; Leichardt, NSW, Australia) [24] and the SMS recall platform called Go Share Plus [25] developed by Healthily (an Australian-based health technology and patient education company). To ensure there will be enough eligible patients, each general practice will have to have at least two full-time equivalent GPs and all GPs will have to agree to consent to allowing their eligible patients to receive the SMS. CAT4 is linked to the EMR and is used to generate lists of patients and their mobile telephone numbers due to receive the NBSCP kit based on the eligibility criteria. The SMS will be sent to patients from the Go Share Plus platform.

#### Inclusion and exclusion criteria for patients

Inclusion criteria are active patients of the general practice aged between 50 and 60 years old and due to receive a NBCSP kit in the next month based on their date of birth or date of completion of the NSBCP kit. NBCSP kits are sent shortly after a person’s 50th birthday and then every 2 years. If a person completes a kit the date for the next kit is 2 years after the date of completion.

An active patient is defined as someone who has at least three episodes of care recorded at the general practice within the previous 2 years [26]. Only active patients are included so that we do not inadvertently send an SMS to patients who have another principal general practice where their NBCSP results are recorded.

Patients will be excluded from the trial if they do not have a mobile telephone number recorded in their EMR record, have opted out of receiving SMS messages from their general practice, or have a diagnosis of CRC recorded in the EMR.

### Who will take informed consent? {26a}

#### General practice informed consent for the trial

The trial coordinator will obtain informed consent from all eligible and interested general practices. The trial coordinator will discuss the trial with the practice staff at a meeting organised by the practice manager. This will be conducted by an electronic meeting system (EMS) (e.g. Zoom), due to the COVID-19 pandemic [27] and associated physical distancing restrictions. The practice manager will be sent the plain language statement and consent form via email following a telephone conversation to discuss SMARTscreen and gauge interest. A Plain Language Statement brochure (Additional Document A) will be sent to all staff in the general practice by Australia Post. The general practice manager and lead GP or their representative will complete the consent form on behalf of the general practice staff, and a signed copy will be sent back to the trial coordinator.

#### Patient informed consent for the trial

Patients will not provide individual consent as no identifying information about the patients will be collected or viewed by the research staff. Patients routinely receive SMS text messaging information and reminders from their general practice unless they individually seek to opt out of receiving information in this way or do not have a mobile number recorded in their EMR.

Patients can also remove themselves from the trial either by informing the practice manager or by using the ‘opt out’ instructions in the SMARTscreen SMS. Only aggregated, de-identified and non-re-identifiable patient data will be included in the study results.

The SMARTscreen trial will be advertised with posters in the waiting rooms of participating general practices to inform people that research is being undertaken in the general practice and they can request more information about this research.

#### General practice staff and patient informed consent for the qualitative interviews

Individual informed consent will be obtained from all interviewees. General practice staff working in intervention general practices who are involved in the delivery of the SMARTscreen intervention will be invited to participate in a semi-structured interview (Additional Document B). They will receive a plain language statement and consent form explaining the purpose of the interview. A trained qualitative interviewer who is not involved in the SMARTscreen trial will contact the general practice staff to obtain informed consent and conduct semi-structured interviews either by zoom or face-to-face depending on interviewees preference.

Intervention group practice managers will invite eligible patients to participate in an interview using a sampling matrix to ensure a range of patients are interviewed based on demographics: location (rural or regional city), age and sex. Patients who consent to be contacted by research staff will be given a Plain Language statement and Consent Form. The trial coordinator will contact consenting patients to obtain informed consent to participate in an interview (Additional Document C) at a time of their choice. All interviews are conducted by trained qualitative interviewers and all interviewees will be re-imbursed for their time with an AUD$50 gift voucher.

### Additional consent provisions for collection and use of participant data and biological specimens {26b}

Not applicable. No biological specimens will be collected.

## Interventions

### Explanation for the choice of comparators {6b}

General practices allocated to the control group will continue their usual care which will include any methods they currently use to promote participation in the NBCSP. Patients’ healthcare will not be compromised, and general practices will continue to support patients who test positive through the NBCSP as per their usual care practice.

### Intervention description {11a}

The SMARTscreen SMS will be sent to eligible patients from general practices in the intervention group in the last week of each month of the 6-month intervention phase. Staff use the CAT4 software, which is linked to the EMR to generate the list of eligible patients using the custom made SMARTscreen filters within CAT4. These filters were designed for the SMARTscreen trial and developed by Pen CS to identify lists of patients by age (patients who are due to turn 50, 52, 54, 56, 58, or 60 years old in the current month), have not had a diagnosis of CRC, and are eligible to receive the NBCSP kit in the next 4 weeks. An additional filter was developed to identify the group of patients aged between 50 and 60 years who have a FOBT result recorded 24 months prior and therefore due to receive a NBCSP kit. GoShare Plus is a recall SMS messaging platform integrated within CAT4 which sends the SMARTscreen SMS to the list of generated patients’ mobile telephone numbers.

#### The SMARTscreen SMS intervention

The SMARTscreen SMS is a text message (Fig. 1) which has an embedded hyperlink to a customised webpage with the four evidence-based health information interventions (Fig. 2). The text message is addressed to the patient (using their first name) and from their general practice.

**Fig. 1 Fig1:**
[figure not shown]
SMARTscreen SMS - test message

**Fig. 2 Fig2:**
[figure not shown]
SMARTscreen SMS. (1) A message from the patient’s GP endorsing the NBCSP. (2) Narrative communication video. (3) An animated video describing step-by-step how to do the NBCSP test. (4) Cancer Council Victoria information about bowel cancer screening and the NBCSP

The ‘opt out’ instructions will also in the text message for patients who no longer want to receive SMS communication from the general practice.

The SMARTscreen intervention webpage includes the following (Fig. 2):
*A message from their GP endorsing the NBSCP*: The message from the general practice includes the patient’s general practice name and logo. The message encourages the patient to do the bowel cancer screening kit and recommends the patient look at the other interventions in the link.*Narrative communication video*: Directly under the GP message the patient can watch a video of a person describing their positive experience of participating in the NBCSP. The running time for this video is 29 s.*An animated video about how to do the NBSCP test*: This animation guides the patient through how to do the kit and send it back using simple step-by-step instructions. This video was produced by the NBCSP and the running time is 2.47 min [4].*NBCSP information*: A hyperlink to the Cancer Council Victoria website providing information about bowel cancer screening and the NBCSP [28].

The SMARTscreen intervention will be co-designed by Healthily and the Investigator team which is made up of a team of health professionals (GPs, nurses, gastroenterologists), primary care cancer researchers, medical software developers and consumer representatives. The consumer representatives were invited to be investigators as they were directly involved in the development of the video messaging based on their experience of CRC. Pretesting of the initial SMARTscreen SMS will be conducted with the Primary Care Collaborative Cancer Clinical Trials Group (PC4 CAG) including their consumer representative group (PC4 CAG) [29], and GP representatives’ group (GP Circle) [30].

### Criteria for discontinuing or modifying allocated interventions {11b}

General practices will be able to withdraw from the SMARTscreen yrial at any time without providing a reason. Patients may elect to not be contacted by SMS, by replying “STOP” to text message or they may withdraw by contacting their general practice. Patients will not be able to withdraw data as all data will be non-re-identifiable and aggregated.

### Strategies to improve adherence to interventions {11c}

The trial coordinator will be in regular contact with general practice staff delivering the intervention. Support will be provided to deliver the intervention each month and collect the aggregated data. The trial coordinator will be in contact with the control group at two time points throughout the trial to collect aggregated, deidentified data. Training and a comprehensive training manual will be provided to maintain consistency and quality of the intervention delivery and data collection across general practices.

### Relevant concomitant care permitted or prohibited during the trial {11d}

There are no interventions that will be permitted or prohibited during the trial. Usual care will continue to be provided in all participating general practices.

### Provisions for post-trial care {30}

The Healthily Go Share Plus messaging platform, the SMARTscreen SMS and training manual will be available to all participating general practices at the conclusion of the trial if the intervention is found to be efficacious. All participating general practice staff will receive a report for the SMARTscreen trial which includes detailed results of the study.

There is minimal risk to patients who receive the SMS. The SMARTscreen recommendations are within the Australian Colorectal Cancer Guidelines [31] and participants will be due to receive a NBCSP kit within a month of receiving the SMS. A poster in the general practice waiting room will inform patients that the general practice is participating in research and some patients aged between 50 and 60 years old will receive an SMS and if they have any questions to discuss this with the practice manager. All SMSs include the general practice telephone number. General practice staff will be trained to provide accurate information about the trial if patients contact their general practice with questions.

### Outcomes {12}

The primary outcome will be the difference in the proportion of eligible patients who completed an FOBT between the intervention and control group for up to 12 months after the SMS was sent as recorded in their EMR.The process measures will be evaluated quantitatively and qualitatively for the intervention group only.

Quantitative process measures collected by age and gender for each general practice will be:
The number of patients sent a SMS;The number of patients sent a SMS and opted out;The number of patients sent a SMS and opened the hyperlink to view the GP message;The number of patients sent a SMS and opened the hyperlink to view the narrative video and how many times they view the narrative video;The number of patients sent a SMS and opened the hyperlink to view the animation of the step-by-step instructions to complete the FOBT and how many times they did this; andThe number of patients sent a SMS and opened the hyperlink and then click on the link to view the NBCSP webpage information and how many times they did this.

Qualitative process measures will be collected using interviews based on Sekhon’s framework for acceptability [32] and Murray’s Normalisation Process Theory [33] to explore feasibility. The interviews will be used to understand if and how the SMS might work in general practice from the practice staff and the patients’ perspectives. This will also provide important information about barriers and facilitators to embedding the SMS into routine clinical practice (Additional Documents B & C).

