## Statistical methods

### Statistical methods for primary and secondary outcomes {20a}

Descriptive statistics will be used to summarise the general practice characteristics, patients age and sex for both trial groups. We will also compare the proportion of active patients aged 50 to 60 years old and due to a NBCSP kit that was excluded because they did not have a mobile telephone number recorded in their EMR record, or opted out of receiving SMS messages from their general practice.

Intention-to-treat analysis will be used, where all general practice allocated to the trial group will be included and analysed in the group they were assigned [37]. The primary outcome will be calculated as the proportion of eligible patients who complete the FOBT up to 12 months following the beginning of the trial intervention for both the intervention and control groups. The primary outcome will be compared between the intervention and control groups using logistic regression and generalised linear model with an identity link function and binomial family to estimate the odds ratio and difference in proportions, respectively. Both regression models will use generalised estimating equations with robust standard errors to allow for clustering by general practice and will adjust for the randomisation stratification factors (geographical remoteness using the Modified Monash Model) and general practice size. Both the relative and absolute measures of the estimated intervention effect will be reported with respective 95% confidence intervals, and a *p* value calculated from the logistic regression model. The intra-practice correlation, which quantifies the proportion of the total variation in the outcome attributable to between-cluster variation in the outcome, will also be estimated using one-way analysis of variance and reported with 95% confidence intervals. Statistical analysis will be conducted using Stata statistical software 15 [38]. Process measures will be summarised as counts and proportions of active patients who opened each of the four intervention components of the SMARTscreen intervention SMS at least once, and how many of the components were opened (none, 1, 2, 3 or 4). We will also summarise the number of times the links to the four interventions were accessed.

Qualitative acceptability and feasibility outcomes will be described by themes from the inductive analysis of interviews with general practice staff and patients.

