## Trial status

We commenced SMARTscreen in 2020 during which the NBCSP continued in Australia despite the COVID-19 pandemic. By October 2020, a total of 21 general practices were recruited to SMARTscreen with an 84% recruitment success. Although our original sample size was 20 general practices, the SMARTscreen trial steering committee agreed to recruit all 21 general practices who expressed interest, to allow for potential attrition. The intervention period commenced in January 2021 and will be completed by the end of July 2021. Data collection will continue until the end of December 2021 and trial results are due in 2022.

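### The primary outcome has two conflicting start points, and neither gives control patients an index date that matches the monthly SMS rounds

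*Protocol article*

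**What the plan says.** Outcomes {12} defines the primary outcome as the between-group difference in the proportion of eligible patients with a completed FOBT, counted "for up to 12 months after the SMS was sent as recorded in their EMR". The Methods paragraph of the abstract uses the same start.

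Statistical methods {20a} instead counts completed tests on a different clock: "up to 12 months following the beginning of the trial intervention for both the intervention and control groups".

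Intervention description {11a} says that the SMS goes out "from general practices in the intervention group in the last week of each month of the 6-month intervention phase". Under Explanation for the choice of comparators {6b}, control practices continue usual care. Plans for assessment and collection of outcomes {18a} has intervention practices collecting data every month and control practices at two points on a 6-monthly schedule.

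Trial status gives the calendar for the sends: "The intervention period commenced in January 2021 and will be completed by the end of July 2021". The same section also fixes when outcome data stop: "Data collection will continue until the end of December 2021".

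**The concern.** This is the trial's only comparative outcome, and its two definitions run on different clocks. One starts for each patient at the message. The other starts once for the whole trial. Because messages go out in monthly rounds, the two clocks drift apart as the intervention phase proceeds, and they can give different numerators for the same patients.

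The message-based clock has no counterpart in control practices. The trial-based clock has one, but it does not say when a given control patient became due. An analyst therefore has to choose a start, and has to decide how control patients are placed into monthly lists. If those choices differ by arm, the arms are counted over different windows and the effect estimate is biased. If they are the same in both arms, the result is still a blend of follow-up lengths that the named horizon does not describe.

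**Working it through.** **Sample size.** The plan's own calculation is not affected by this point, and it reproduces. For 50% against 40%, with 80% power, two-sided 5% and continuity correction, the requirement is 408 per arm. The design effect is 1 + (70 − 1) × 0.008 = 1.552. Then 408 × 1.552 / 70 = 9.05, rounded up to 10 practices per arm, and 20 × 70 = 1400.

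**Step 1: which start exists in which arm.**

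| Rule | Start | Intervention patient | Control patient |
|---|---|---|---|
| Abstract, Outcomes {12} | SMS sent | Date of the patient's round | None: no SMS is sent |
| Statistical methods {20a} | Beginning of the trial intervention | One trial-level date, day not given | The same trial-level date |

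**Step 2: follow-up from the SMS.** The inputs are sends in the last seven days of a month in 2021 and a cut-off of 31 December 2021. Months = days from send to cut-off / 30.4375.

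| Round | Send dates | Days | Months |
|---|---|---|---|
| January | 25–31 | 334–340 | 10.97–11.17 |
| February | 22–28 | 306–312 | 10.05–10.25 |
| March | 25–31 | 275–281 | 9.03–9.23 |
| April | 24–30 | 245–251 | 8.05–8.25 |
| May | 25–31 | 214–220 | 7.03–7.23 |
| June | 24–30 | 184–190 | 6.05–6.24 |
| July, if sent | 25–31 | 153–159 | 5.03–5.22 |

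No round reaches 12 months. Provisions for post-trial care {30} puts the kit within a month after the SMS, so time with the kit in hand can be up to a month shorter.

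**Step 3: follow-up from the beginning of the intervention.** The day in January is not stated, so it is an assumption. Counting both end dates: from 1 January, 365 / 30.4375 = 11.99 months; from 25 January, 341 / 30.4375 = 11.20; from 31 January, 335 / 30.4375 = 11.01. This rule gives about 11 to 12 months.

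**Step 4: how far the two clocks diverge.** For a June send, the trial clock has already run 340 − 190 = 150 days (4.9 months) if it began with a January round in the last week of the month. If it began on 1 January, it has run 174 to 180 days (5.7 to 5.9 months). During that time the patient was neither messaged nor listed as due.

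**Step 5: number of rounds.** January to end July contains seven month-ends, while {11a} describes a 6-month phase. In whole months, and assuming lists of equal size, mean follow-up from the SMS is:
- January–June: (11 + 10 + 9 + 8 + 7 + 6) / 6 = 8.5
- February–July: (10 + 9 + 8 + 7 + 6 + 5) / 6 = 7.5
- January–July: (11 + 10 + 9 + 8 + 7 + 6 + 5) / 7 = 8.0

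**Step 6: listing in control practices.** Intervention lists are built each month. The article does not say whether control lists are also built by month, or only at the two collection points in {18a}. Nothing in it ties a control patient to a round.

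**The case against.** Three stronger readings are tempting, and the documents do not support them.

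A reader might infer that controls have no start date at all. They do: {20a} expressly applies its rule to both groups, and a calendar date works for controls. What is missing is an index date that matches the monthly rounds.

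A reader might infer that no patient can have 12 months under any rule, or that the plan breaks a promise of 12 months. From the beginning of the intervention the cut-off allows about 11 to 12 months. Every statement of the horizon sets an upper limit, so shorter follow-up does not contradict the wording.

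A reader might infer that the comparison is biased. No section proposes different rules by arm. With a common rule and month-by-month eligibility in both arms, follow-up varies by round but should be similar between arms. That blurs what is being estimated and may change the size of the effect, but it does not by itself bias it.

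Two further points on the other side stand in part. Under the patient eligibility criteria {10}, completing a kit moves the next due date to 2 years later. If eligibility is applied month by month, someone who completes a kit after trial start but before listing would drop off the list. Counting FOBTs from before listing may therefore matter little; its size cannot be derived here, and it depends on how control lists are built. The 5-month figure rests on a July send, which sits badly with a 6-month phase.

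The participant timeline (Table 1) is not shown and might state windows. It could not remove the conflict between {12} and {20a}.

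**Conclusion.** The point holds in a limited form. The primary outcome is defined with two start points that cannot both be used. One does not exist for control patients, and the other can precede a patient's due date by roughly 5 to 6 months for a June list. No control index date mirrors the monthly rounds, and the data collection schedules differ by arm.

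From the SMS, follow-up at the end of December 2021 falls from about 11 months (January) to about 6 (June), or about 5 if a July round took place. It therefore differs about two-fold between rounds, and no SMS recipient has 12 months. From the beginning of the intervention it is about 11 to 12 months. These figures assume sends in the last seven days of the month and a cut-off of 31 December 2021.

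The defect is an ambiguous outcome with unequal windows. Bias between arms is a risk that the wording leaves open, not something the plan commits to. Because this is the only comparative outcome, it should be settled before the data are analysed.

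**What to change.** Use one definition in the abstract, Outcomes {12} and Statistical methods {20a}:

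- **Index date:** the end of the calendar month in which the patient first meets the SMARTscreen due-for-kit filter, applied identically in both arms. Control lists are built, or reconstructed, by month.
- **Outcome:** an FOBT dated after the index date and within a fixed number of months, the same for every list and both arms.
- **Window:** either keep the December 2021 cut-off and name the window that every list completes (6 months if the last send is June, 5 if July), or make the final CAT4 extraction 12 months after the last send.
- **Calendar:** reconcile the 6-month phase with January to end July, and state the number of rounds.

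The cost is wording, date-limited CAT4 filters by list month in control practices, and either a shorter stated follow-up or one later extraction per practice. Data can stay aggregated, as counts by list month. No extra patients are needed. No interim analysis is planned and the statistician works from coded groups, so the rule can be fixed without knowledge of results.
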